## Abstract

**Background:**

Globally COVID-19 has had a profound impact on the psychological wellbeing of millions of people, and there is an urgent imperative to address elevated levels of distress during the COVID-19 pandemic. The World Health Organization (WHO) has developed Problem Management Plus (PM+), a low intensity psychological intervention for adults experiencing psychological distress. This paper outlines the study protocol for a trial that tests the effectiveness of an adapted version of PM+ to reduce distress associated with COVID-19.

**Methods:**

A single-blind, parallel, randomized controlled trial will be carried out for distressed people across Australia. via video conferencing on a small group basis. Following informed consent, adults that screen positive for levels of psychological distress (General Health Questionnaire-12 (GHQ-12 score ≥ 3) and have access to videoconferencing platform will be randomised to an adapted version of gPM+ (*n* = 120) or enhanced treatment as usual (ETAU) (n = 120). The primary outcome will be reduction in psychological distress including anxiety and depression at 2-months post treatment. Secondary outcomes include worry, sleep problems, anhedonia, social support, and stress in relation to COVID-19.

**Discussion:**

The trial aims assess whether an adapted version of videoconferencing PM+ that is specifically designed to target COVI-19 related distress will result in reduced distress relative to enhanced usual care.

**Trial registration:**

This trial was prospectively registered on the ANZCTR on 14/4/20 (ACTRN12620000468921).

## Article summary

### Strengths and limitations of the study

This is the first controlled trial of a videoconferencing psychological intervention to reduce psychological distress during COVID-19.This design is novel in that it provides remote delivery and is group-based which affords potentially cost-effective mental health intervention in situations of lockdowns.This trial conducts blind assessments of all participants at baseline, post-intervention, 2-month follow-up, and 6-month follow up via online assessments.Structured clinical interviews were not conducted to ascertain mental disorders.The study does not provide long-term follow-up assessments beyond 6 months, thereby limiting conclusions about longer-term benefits.

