## Methods

### Aim and design

This study aims to evaluate the effectiveness of an adapted version of PM+ to specifically target COVID-19 related distress in reducing anxiety and depression. We will conduct a two-arm single-blind, parallel, randomized controlled trial (RCT) comparing PM+ with enhanced treatment as usual (ETAU) in 240 participants (see Fig. 1 for an overview of the design, following the Standard Protocol Items: Recommendations for Intervention Trials (SPIRIT [14];). This trial adhered to the trial protocol (version 2, April 10, 2020). The study design will employ a 2 (Treatment Condition) × 4 (Assessment Point) factorial design. Participants will be assessed at baseline, post-intervention, and two- and six-month follow-ups. The primary outcome time point is the two-month assessment, and the primary outcome is anxiety and depression. Secondary outcomes include worry, sleep impairment, positive and negative mood, anhedonia, and COVID-19-related concerns.

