### Procedure

Following receipt of consent, participants will be directed to a webpage that that will include the General Health Questionnaire (GHQ). If participants score ≥ 3 on the GHQ they will be randomized to either PM+ or ETAU. If participants are not selected because they score below the cut-offs for the GHQ-12, they will be provided feedback on their test outcomes and reasons why they are not eligible for the study will be explained to them. If participants meet any of the exclusion criteria, participants will be referred to seek support from their local physician for further management with specialised services. Participants will then be directed to an online assessment batter, which will include the Hospital Anxiety and Depression Scales (HADS), Generalized Anxiety Disorder Scale (GAD-7), Sleep Impairment Index (SII), and Positive and Negative Affect Schedule (PANAS), Pleasure Scale (PS), Coronavirus Stress Scale (CSS). This online assessment, which will be repeated at post-treatment and 2-month follow-up will ensure independent assessments because no research personnel will administer these. Participants were reimbursed $50 if they completed all assessments.

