#### Enhanced treatment-as-usual (ETAU)

Participants in the ETAU arm will be emailed a resource package comprising handouts detailing the strategies taught in PM+, with instructions to work through in a self-paced manner across the course of a six-week duration. Those randomized to the ETAU arm will not receive support from a clinical psychologist/group facilitator.

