### Primary outcome

The primary outcome will be severity of anxiety and depressive symptoms as measured using the Hospital Anxiety and Depression Scales (HADS [17]). The HADS is a 14-item scale consisting of two sub-scales: HADS-A (Anxiety, 7 items, range 0–21) and HADS-D (Depression, 7 items, range 0–21). Higher scores indicate more severe anxiety and/or depression. The minimal clinically important difference has been determined at 1.32 for HADS-A and 1.40 for HADS-D [18].

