### Data management

Adverse events will be monitored at each assessment. Any adverse events that occur during the trial involving untoward medical or psychological occurrence in a participant that is related to the trial will be reported in the study on a standard form and submitted to the study’s Data Monitoring Committee and Trial Sponsor. These adverse reactions will be referred to appropriate services and the relevant psychologist managing this case will follow up at 1 month.

As this is a treatment trial, participants will be required to have their identities known to the study because they are seen on a weekly basis, and then be contacted for follow-up assessment. All data entered by participants during the online surveys collected at pretreatment, posttreament, and follow-up will be entered on an electronic database in a deidentified manner in which participants are allocated a unique identification number. Access will be restricted to research staff directly involved in the study. If the data is moved to any other computer location it will have AES-256 bit encryption. We routinely audio record group therapy sessions in line with CONSORT requirements for subsequent testing of treatment fidelity via independent coding of experts. The research staff working on the project will initially have access to the data via the UNSW Research Long Term Data Store Interface.

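### Assessments described as blind are self-reported by participants in visibly different arms, so after baseline they are free of interviewer influence but not blind to allocation

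*Protocol article*

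**What the plan says.** Under Strengths and limitations of the study, the article states: "This trial conducts blind assessments of all participants at baseline, post-intervention, 2-month follow-up, and 6-month follow up via online assessments". The Abstract and the Aim and design section both call the trial single-blind; the latter reads "We will conduct a two-arm single-blind, parallel, randomized controlled trial (RCT) comparing PM+ with enhanced treatment as usual (ETAU) in 240 participants". Neither place says who is blinded.

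The only supporting reason is in Procedure, where the online battery "will ensure independent assessments because no research personnel will administer these". On the outcomes themselves:

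- **Primary outcome:** "The primary outcome will be severity of anxiety and depressive symptoms as measured using the Hospital Anxiety and Depression Scales".
- **Data management:** the section refers to "All data entered by participants during the online surveys collected at pretreatment, posttreament, and follow-up".
- **Strengths and limitations:** "Structured clinical interviews were not conducted to ascertain mental disorders".

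The arms are described under Introductory online session and Interventions. PM+ participants have a short video introduction with their facilitator, then six weekly hour-long video groups of three or four people led by a clinical psychologist. ETAU participants are emailed handouts covering the same strategies, to use at their own pace over six weeks: "Those randomized to the ETAU arm will not receive support from a clinical psychologist/group facilitator".

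**The concern.** Blinded outcome assessment means that whoever produces the rating does not know the allocation. With a self-completed symptom scale, the participant produces the rating. Taking the interviewer away removes one source of influence, but it leaves the respondent's own knowledge of the treatment in place. The article moves from no staff administering the form to the assessments being blind, and the second does not follow from the first.

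This matters because the primary endpoint is a subjective scale, and the comparison is between live contact with a psychologist and unsupported self-help. How participants feel about what they received can affect their answers apart from any change in symptoms. A reader or a risk-of-bias rater who relies on the summary may credit the trial with protection against this. The limitations in the same list do not mention unmasked self-report.

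**Working it through.** The article gives no figure for blinding, so the check is to set its statements side by side.

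**Step 1. Who rates the outcomes?** Table 1 lists six outcome instruments: HADS (primary), GAD-7, the sleep index, PANAS, the COVID stress scale and the Pleasure Scale. Procedure places all six in the online battery with no research staff administering it. Data management says that participants enter the data. The summary says no structured diagnostic interviews were done. One remark under Secondary outcomes explains the shortened sleep measure by the time limits of a larger clinical interview. That sits awkwardly with the rest, but no interviewer-rated outcome is listed anywhere. The rater is the participant for six of six instruments.

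**Step 2. Can the rater tell which treatment was given?** Under Recruitment and informed consent, participants read an explanation of the trial before consenting. They then receive either live facilitated groups or emailed handouts with no facilitator. The article describes no masking of participants, and the two formats cannot be mistaken for each other. That participants know what they received is an inference, but a near-certain one.

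**Step 3. Which time points are affected?**

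| Time point | Staff influence removed? | Rater unaware of treatment received? |
|---|---|---|
| Baseline | yes | possibly |
| Post-treatment | yes | no |
| 2 months (primary) | yes | no |
| 6 months | yes | no |

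Baseline is uncertain. Procedure describes the battery after randomisation, but the article does not say when participants are told their arm. The other three points all follow six weeks of treatment. The statement that assessments are blind therefore fails at 3 of 4 points, which is 6 × 3 = 18 of the 6 × 4 = 24 scheduled instrument administrations.

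**Step 4. Does this touch the sample size?** No. At effect size 0.5, power 0.95 and two-sided alpha 0.05, the two-sample t-test needs 104.93, so 105 per arm, as the Analysis section states. Allowing for 10% attrition, 105 / 0.9 = 116.7, so 117 per arm or 234 in total. The planned 240 leaves 120 × 0.9 = 108 per arm. None of these figures depends on blinding, and none is in dispute.

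**The case against.** Several parts of the case for the article stand.

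- **Independence from staff is real.** Procedure claims only that assessments are independent because staff do not administer them. That is true and worth having. A reader might infer that the design offers no protection at all, which would be wrong.
- **The mechanism is disclosed.** The summary sentence itself says the assessments are online, and the arms are fully described. A careful reader can classify the outcomes correctly. This limits the harm but does not make the word blind accurate.
- **Single-blind may refer to someone else.** The article condenses a fuller protocol (version 2, April 2020). That document or an analysis plan may name a masked party, such as the analyst. A reader might infer that nobody in the trial is blinded; the article's silence does not show that.
- **ETAU is an active comparator.** Its participants get the PM+ strategies as self-help. Whether they regard it as the control, or know the hypothesis, depends on the trial explanation, which is not shown. A reader might infer that reporting bias must favour PM+, or might attach a size to it. The direction is plausible, but the documents state neither direction nor size.
- **Participants cannot be masked to live groups versus handouts.** Agreed. The fault is in the description, and no change of design is implied.

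Appeal to a fuller document does not rescue the summary sentence. It makes a positive statement about the assessments, and the statement stays inaccurate as long as the outcomes are self-reported by people who know what they received.

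**Conclusion.** The point holds as a correction to a stated property of the trial. At post-treatment, at the 2-month primary time point and at 6 months, all outcomes are free of interviewer influence but not blind to allocation. Baseline may be unaffected. The conclusion rests on one assumption, that participants recognise which of two visibly different treatments they received. No numerical bias can be derived from the documents, and the sample size stands. The correction is worth making because it concerns what the trial can claim about a main source of bias in its primary outcome.

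**What to change.** 1. In Strengths and limitations of the study, replace the reference to blind assessments with wording such as *participant-reported outcomes collected online without staff involvement, not blinded to allocation*.
2. In the same list, add unmasked self-report as a limitation on interpreting the HADS effect.
3. In the Abstract and in Aim and design, either name the party who is blinded or drop the term single-blind.

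The statement in Procedure about independence from research staff can stay. Only wording changes: design, outcomes, sample size and conduct are untouched. The cost is the loss of a claimed strength.

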## Background

The COVID-19 pandemic, caused by severe acute respiratory syndrome coronavirus 2, has had a profound global impact, and represents the most severe global health threat in recent pandemic history. Concerns about COVID-19 are pervasive and have several serious adverse impacts on hospital systems, health workers and the general community. A pandemic of this nature with the associated uncertainty including lockdowns, physical distancing and other quarantine measures has been shown to involve a significant psychological burden on many people. Many studies conducted during the COVID-19 pandemic have highlighted the elevated rates of common mental disorders, with systematic reviews and meta-analyses of studies conducted throughout the pandemic indicate that between one-quarter to one-third of people in affected communities may be experiencing these conditions [1–4]. For example, one meta-analysis indicated that the pooled prevalence of depression, anxiety, psychological distress, and insomnia was 31.4, 31.9, 41.1, and 37.9%, respectively [2]. Various factors have been shown to increase the risk of psychological problems during the pandemic, including being female, younger, lower socioeconomic status, living in rural areas, in quarantine or lockdown restrictions, infected with the virus [2, 5], There is also much evidence that frontline health workers are also at higher risk for common mental disorders [6–8].

There is an urgent imperative for scalable programs that can address the pervasive psychological distress experienced by people during the COVID-19 pandemic. In the light of need for physical distancing and evolving lockdown and quarantine measures, these programs need to be delivered in an easily accessible format that can accommodate social distancing requirements and that can also achieve considerable reach across communities. One possible strategy is the Problem Management Plus (PM) + that has been developed by the World Health Organisation (WHO) in collaboration with the University of New South Wales (UNSW) [9]. This is a 5-session scalable intervention designed to reduce stress, anxiety and depression in the wake of crisis and adversity. It comprises evidence-based techniques of problem solving, stress management, behavioral activation, and accessing social support [10]. This program is suitable for the current needs during COVID-19 because PM+ strategies are simple to learn, are transdiagnostic and address diverse features of psychological distress, and can be taught in brief format. The intervention was developed to be delivered by a range of trained personnel, including those with no specialist mental health qualifications. PM+ has been evaluated in various setting and shown to reduce mental distress and promote general functioning in those exposed to ongoing adversity, and has been shown to be effective when delivered in individual [11, 12] or group [13] formats.

The goal of the current study is to test the effectiveness of an adapted version of PM+ specifically designed to target COVID-19 related distress and coping in the face of ongoing uncertainty and unpredictability of the current situation. We predict that PM+ would lead to greater reductions in anxiety and depression relative to enhanced usual care, as well as reduced worry, sleep disturbance, positive and negative mood, hedonia, and COVID-19 related concerns.

## Methods

### Aim and design

This study aims to evaluate the effectiveness of an adapted version of PM+ to specifically target COVID-19 related distress in reducing anxiety and depression. We will conduct a two-arm single-blind, parallel, randomized controlled trial (RCT) comparing PM+ with enhanced treatment as usual (ETAU) in 240 participants (see Fig. 1 for an overview of the design, following the Standard Protocol Items: Recommendations for Intervention Trials (SPIRIT [14];). This trial adhered to the trial protocol (version 2, April 10, 2020). The study design will employ a 2 (Treatment Condition) × 4 (Assessment Point) factorial design. Participants will be assessed at baseline, post-intervention, and two- and six-month follow-ups. The primary outcome time point is the two-month assessment, and the primary outcome is anxiety and depression. Secondary outcomes include worry, sleep impairment, positive and negative mood, anhedonia, and COVID-19-related concerns.

**Fig. 1 Fig1:**
[figure not shown]
Flow diagram of study

### Setting

PM+ will be delivered via a video teleconferencing format for community-based people across Australia.

### Participants

articipant inclusion criteria are a) adult (18 years or older); b) score ≥ 3 on the General Health Questionnaire-12; GHQ-12 [15]); and (c) report sufficient English language comprehension. Exclusion criteria are: a) current psychosis; b) imminent suicidal risk; c) current substance dependence (but not abuse); or d) no internet-based access for teleconferencing.

### Recruitment and informed consent

Potential participants will be recruited for the study portal at the UNSW Traumatic Stress Clinic (http://www.traumaticstressclinic.com.au/). The study will be advertised via online media and Facebook. The investigators will make no direct contact with potential participants prior to their approach to the clinic. Individuals who express interest in taking part in the study will read an explanation of the trial, and then provide informed consent by indicating consent via digital endorsement on the trial website.

### Procedure

Following receipt of consent, participants will be directed to a webpage that that will include the General Health Questionnaire (GHQ). If participants score ≥ 3 on the GHQ they will be randomized to either PM+ or ETAU. If participants are not selected because they score below the cut-offs for the GHQ-12, they will be provided feedback on their test outcomes and reasons why they are not eligible for the study will be explained to them. If participants meet any of the exclusion criteria, participants will be referred to seek support from their local physician for further management with specialised services. Participants will then be directed to an online assessment batter, which will include the Hospital Anxiety and Depression Scales (HADS), Generalized Anxiety Disorder Scale (GAD-7), Sleep Impairment Index (SII), and Positive and Negative Affect Schedule (PANAS), Pleasure Scale (PS), Coronavirus Stress Scale (CSS). This online assessment, which will be repeated at post-treatment and 2-month follow-up will ensure independent assessments because no research personnel will administer these. Participants were reimbursed $50 if they completed all assessments.

### Randomization

This randomization be conducted by a computerized software on a 1:1 basis. A research assistant at UNSW who is independent of any other aspects of the treatment study will allocate individuals into the group they are randomized into and invite them for the introductory online session with the group facilitator.

### Introductory online session

Following informed consent, those randomized to the PM+ will be contacted to participate in an initial 10–15 min introductory online session with their group facilitator to explain technological issues involved in using the online teleconferencing platform, and other basic information relating to how the group intervention will operate.

### Interventions

#### Problem management plus (PM+)

The WHO PM+ programme is a brief psychological intervention that seeks to reduce symptoms of stress (e.g. depression, anxiety) for those affected by ongoing adversity. This program was adapted to include evidence-based strategies that specifically target COVID-19 related distress. This includes education about common reactions to COVID-19, stress management, structured problem solving, worry management, behavioural activation and skills to strengthen access to social support. Finally, relapse prevention will involve teaching participants relapse prevention techniques, including identification of possible future relapse situations and rehearsal of strategies to manage these situations. PM+ content was adapted to expand its content to address excessive worries because the nature of the pandemic is that distress can be heightened by worries about health of self and others, employment security, and financial stress, as well adapting the content to manage loss of normal activities during lockdowns and limited access to use social supports. This adapted version of PM+ is delivered over 6 weekly sessions of 60-min duration. In this RCT, PM+ will be delivered in anticipated group size of 3–4 participants via a videoconferencing platform. PM+ group facilitators will be Masters or Doctoral trained clinical psychologists.

Adherence to PM+ protocol will be ensured by weekly group supervisions including the group facilitators and supervisors. To evaluate treatment fidelity, treatment sessions will be audiotaped and 10% of all PM+ sessions will be independently rated for adherence by two independent clinical psychologists. Raters will be required to nominate what therapy components were present in each session and the quality with which these components were administered.

